### Cost-Effectiveness Analysis

We will estimate the incremental cost of the intervention per DALY averted, with DALYs reflecting the present value of future years of healthy life lost to morbidity/disability and future years of life lost to premature mortality. The incremental cost will be the net total cost of the intervention, excluding the cost of standard-of-care comparison condition.

This study has a multifaceted intervention design, and the emphasis of the cost-effectiveness analysis will be on the incremental cost-effectiveness of PrEP use relative to the intervention components that are not tied to PrEP use. The cost-effectiveness analysis will be in accordance with the recommendations set forth in the US Public Health Service Panel on Cost-Effectiveness in Health and Medicine [32]. We will estimate the additional cost of PrEP use versus PrEP nonuse, number of infections averted through PrEP use, discounted treatment costs saved through PrEP use, and the discounted DALYs averted through PrEP use. On the basis of these estimates, we will determine whether the use of PrEP relative to the standard intervention is cost-saving, cost-effective, or not cost-effective using societal and provider perspectives [32,35,36].

Through the primary outcomes analyses, the number of infections averted will be estimated as the difference between the number of infections that would have been expected without PrEP treatment and the observed number of infections under PrEP treatment.

Treatment costs saved per infection averted will be based on national or local estimates of costs per year for ART in Thailand, including costs for first- and second-line ARVs, laboratory tests, facilities, staff time, and opportunistic infections [44]. Total lifetime treatment costs per HIV infection will be based on remaining life expectancy and disease progression and discounted at 3% per annum [32,45].

DALYs, calculated following the methods of Fox-Rushby and Hanson [46] and Larson [47], will capture the years of life lost and disability associated with HIV infection and will be based on both the difference in life expectancy with and without HIV infection and the difference in the quality of life during years of life not lost. Future DALYs averted will be discounted at 3% per year annum.

The incremental cost-effectiveness ratio (ICER) will be based on the estimation of incremental cost (difference between the additional intervention cost and the additional treatment cost averted) divided by the DALYs averted. The intervention will be considered cost-saving if the additional intervention cost is less than or equal to the additional treatment cost averted, considered highly cost-effective if the ICER is less than gross domestic product (GDP) per capita in Thailand, cost-effective if the ICER is between 1 and 3 times GDP per capita, and not cost-effective if ICER is more than 3 times GDP per capita [48].

For the various cost-effectiveness ratio components, uncertainty intervals will be established based on primary data collection, literature reviews, and expert opinion. One-way and multivariate sensitivity analyses will be used to examine the robustness of the cost-effective estimates. In these analyses, parameters will be varied within the uncertainly intervals, and the resulting estimates will be reported. These components are expected to include estimates of resources consumed, resource costs, discount rates, treatment costs, DALYs per HIV infection averted, and infections averted. In addition, some research procedures may conceivably contribute to an intervention effect, such as monthly PrEP pill counts and weekly SMS adherence surveys. The impact of these procedures on cost estimates and cost-effectiveness will also be evaluated in sensitivity analyses.

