### Intervention Effectiveness Study Design

The study is an open label, nonrandomized assessment comparing the relative effectiveness of a combination preventive intervention with and without daily oral tenofovir/emtricitabine (FTC; Truvada) PrEP with adherence support. We follow those young MSM and TGW who choose to initiate PrEP as part of the combination package, and those who agree to participate but do not choose to start on PrEP, for whom all other intervention components will be offered. The outcome will be assessed using a person-time approach, assessing HIV incidence densities among young MSM and TGW on and off daily oral PrEP over 12 to 24 months of follow-up. Participants are enrolled for a standard follow-up period of 12 months; however, given the importance of remaining on PrEP for people in high-risk contexts, we offer the option to re-enroll for an additional 12 months. All participants, regardless of PrEP status complete quarterly study visits and weekly, brief behavioral SMS surveys. Participants who initiate PrEP are required to attend monthly medication pickup visits. Figure 1 displays the flow diagram of the study with a brief description of study visit activities.

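### The ICER values infections averted during 12 to 24 months at full lifetime cost and DALYs, with no term for later infection or continued PrEP cost; this element favours PrEP

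*Protocol article*

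**What the plan says.** All references are to the protocol article.

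- **Infections averted.** Under Cost-Effectiveness Analysis, "the number of infections averted will be estimated as the difference between the number of infections that would have been expected without PrEP treatment"; the term subtracted is the count observed under PrEP. Both come from the primary outcome analyses. Under Intervention Effectiveness Study Design, those analyses compare incidence "over 12 to 24 months of follow-up". The same section adds: "Participants are enrolled for a standard follow-up period of 12 months", with an optional second year.
- **Value of each infection.** Treatment cost is lifetime: "Total lifetime treatment costs per HIV infection will be based on remaining life expectancy and disease progression and discounted at 3% per annum". DALYs rest on "the difference in life expectancy with and without HIV infection" together with the difference in quality of life. "Future DALYs averted will be discounted at 3% per year annum".
- **ICER.** The numerator is the "difference between the additional intervention cost and the additional treatment cost averted" and the denominator is DALYs averted. The result is classified as cost-saving, or by comparison with 1 and 3 times GDP per capita.
- **PrEP cost.** Cost Analysis Data Collection estimates an incremental cost per person-year on PrEP. Nothing in the article projects that cost beyond the study.
- **Sensitivity analyses.** One-way and multivariate analyses are planned over uncertainty intervals. "These components are expected to include estimates of resources consumed, resource costs, discount rates, treatment costs, DALYs per HIV infection averted, and infections averted". Time horizon and infection risk after PrEP are not named.

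**The concern.** The two sides of the ratio run over different horizons. PrEP cost and infections averted accrue during study person-time, while the value of each infection runs over a lifetime. An averted infection earns the full lifetime credit only if that person is never infected later, at no further PrEP cost. If PrEP ends, some infections are delayed rather than averted. If PrEP continues, its later cost is missing. Either omission lowers the ICER.

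The protocol's own facts make later infection plausible. Participants are 18 to 26 years old, planning incidence is 5 to 11 per 100 PY, and participants may stop PrEP at any time. Aim 3 assigns PrEP to a cost-effectiveness category, and Setting and Context says such analyses are wanted for national policy. A shift that crosses a cut-off would therefore matter.

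**Working it through.** The article states no cost, DALY or ICER, so there is no figure to reproduce. The check asks what share of the lifetime credit survives if people spared in the study remain at risk afterwards.

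**Inputs from the article.** Off-PrEP incidence λ = 5, 8.5 and 11 per 100 PY, a 50% reduction on PrEP (Sample Size Calculation), 620 PY on PrEP (Abstract), and discounting at 3% a year.

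**Assumptions not in the article.** Years at further risk after the study; a low case of λ = 2 per 100 PY; remaining lifetime T of 30 to 50 years; the same discounted shape for DALYs as for treatment costs.

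**Step 1. Planned infections averted.** 620 × 0.085 = 52.7 expected; 620 × 0.0425 = 26.35 observed; 52.7 − 26.35 = 26.35 averted.

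**Step 2. Later infection over 5 further years.** Share infected = 1 − exp(−5λ).

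| λ per 100 PY | Infected later | Still averted |
|---|---|---|
| 5 | 1 − exp(−0.25) = 22% | 20.5 |
| 8.5 | 1 − exp(−0.425) = 35% | 17.2 |
| 11 | 1 − exp(−0.55) = 42% | 15.2 |

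**Step 3. Share of discounted credit that is real, simple form.** Delay has some value through discounting. If a later infection costs the same as an earlier one apart from discounting, over W years:

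share = 1 − [λ/(λ + 0.03)] × [1 − exp(−(λ + 0.03)W)]

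For λ = 0.085 and W = 4: 1 − 0.739 × (1 − exp(−0.46)) = 1 − 0.739 × 0.369 = 0.73.

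| λ per 100 PY | W = 4 | W = 10 |
|---|---|---|
| 5 | 0.83 | 0.66 |
| 8.5 | 0.73 | 0.50 |
| 11 | 0.66 | 0.41 |

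**Step 4. The same share, allowing fewer remaining years after a later infection.** With A(x) = (1 − exp(−0.03x))/0.03 and H years at risk:

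share = 1 − ∫₀ᴴ λ exp(−λt) exp(−0.03t) A(T − t)/A(T) dt

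| λ per 100 PY | H = 2 | H = 5 | H = 10 |
|---|---|---|---|
| 2 | 0.96 | 0.91–0.92 | 0.85–0.86 |
| 5 | 0.91 | 0.80 | 0.67–0.69 |
| 8.5 | 0.85 | 0.68–0.69 | 0.51–0.54 |
| 11 | 0.81 | 0.61–0.62 | 0.43–0.46 |

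Ranges are over T = 30 to 50. The two forms agree closely. Over 4 to 5 years at 5 to 11 per 100 PY the share is about 0.62 to 0.83.

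**Step 5. Effect on the ICER.** Let C be the intervention cost, S the credited treatment saving, D the credited DALYs and s the true share. The planned ICER is (C − S)/D; the corrected one is (C − sS)/(sD) = (C/s − S)/D. Since (C/s − S) − (C − S)/s = S(1/s − 1) ≥ 0, a positive ICER rises by at least 1/s. At 8.5 per 100 PY over 5 years that is at least 1/0.69 = 1.45-fold.

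**The case against.** - **An article condenses the plan.** It never says in words that protection is lifelong, and time horizon and model structure are often left to the full plan. A reader might infer that the investigators have adopted lifelong protection as an explicit assumption; the article does not say so. But the point does not rest on silence. The valuation rule and the ICER formula are stated, and followed as written they give full credit.
- **Sensitivity analyses.** The list of components is open-ended and includes infections averted and DALYs per infection averted. Lowering either would mimic the correction numerically, so the planned analyses could absorb part of the effect. Later infection is not named as a reason to lower them, however, and ranges set around a full-credit base case do not target an error that runs in one direction.
- **Net direction.** A reader might infer that the ICER as a whole is too favourable. The documents do not support that. Onward infections averted are also uncounted and work the other way, and no cost or DALY figure is given from which to net the two. For the same reason, a change of category is possible but not shown.
- **Size.** Holding 8.5 or 11 per 100 PY constant for 10 years leans high. The article gives a lower rate for ages 22 to 26 and describes the early period of exchanging sex as the riskier one. Free government PrEP may also keep some people protected, but then its cost should be counted. This stands, so the 10-year figures should be read as an outer bound.
- **Source of post-study risk.** The study's off-PrEP estimate will be sparse and self-selected. The article reports 33 PY of non-use by February 2019, about 33 × 0.085 = 2.8 expected infections, and the Discussion anticipates too little such time. It cannot be the only input.

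**Conclusion.** The concern holds as a statement about one element of the analysis: crediting in-study infections averted with lifetime value, without later infection or continued PrEP cost, biases the ICER in PrEP's favour. The 62% to 83% range assumes that PrEP ends with the study, that risk continues for 4 to 5 years at the planning rates, and that DALYs follow the same discounted pattern as treatment costs. The 4% loss at 2 per 100 PY for 2 years shows how far the size depends on post-study risk, which the article does not give. The overall direction of bias in the ICER remains open. The change is worth making because the output is a policy category and the correction is inexpensive.

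**What to change.** In the sensitivity-analysis paragraph of Cost-Effectiveness Analysis, add two structural scenarios:

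1. **PrEP ends with the study.** Credit averted infections net of later acquisition, over stated risk periods and a range of post-study incidence. The range could be the planning values of 5 to 11 per 100 PY plus a lower value, informed by the study's off-PrEP estimate but not resting on it alone.
2. **Protection continues.** Carry the PrEP cost per person-year forward over the same period.

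Report the ICER category under each. Label the lifetime-credit result as assuming no later infection, and state that onward transmission is omitted.

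The cost is a small extension of the model, using planning rates and a unit cost already in the plan. The downsides are one more stated assumption (the length and level of post-study risk) and possibly a less favourable ICER.

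### The cost-effectiveness rule sets no condition on the sign of DALYs averted, so a costlier and less effective PrEP result would be labelled 'highly cost-effective'

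*Protocol article*

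**What the plan says.** All of this stands in the protocol article under Cost-Effectiveness Analysis.

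- **Effect.** Infections averted come from the primary outcome analyses, as "the difference between the number of infections that would have been expected without PrEP treatment and the observed number of infections under PrEP treatment". DALYs averted and treatment cost averted follow from that number.
- **Ratio.** The ICER is the incremental cost ("difference between the additional intervention cost and the additional treatment cost averted) divided by the DALYs averted").
- **Classes.** "The intervention will be considered cost-saving if the additional intervention cost is less than or equal to the additional treatment cost averted". It is "considered highly cost-effective if the ICER is less than gross domestic product (GDP) per capita in Thailand", cost-effective from 1 to 3 times GDP per capita, and "not cost-effective if ICER is more than 3 times GDP per capita".
- **Uncertainty.** In one-way and multivariate sensitivity analyses, "parameters will be varied within the uncertainly intervals, and the resulting estimates will be reported". Infections averted is one of the components to be varied.

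Neither this section nor the statement of Aim 3 in the Methods summary has a class for a dominated result or a condition on the sign of DALYs averted.

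**The concern.** A cut-off on a ratio orders results correctly only while the denominator stays positive. Infections averted is an estimated difference and can fall below zero. The ratio then changes sign, and a worse result lands under the most permissive of the three ICER cut-offs. The section sets out a full set of classes with numerical limits, so this is a stated rule that returns a wrong answer, not a detail left for later.

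Aim 3 exists to deliver this classification, and Setting and Context says that cost-effectiveness analyses are wanted to support policy on government-funded PrEP. A pre-specified rule should not give the same label to a good result and to a harmful one.

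**Working it through.** **1. The sign, from the text alone.** Let A be infections averted, D > 0 the DALYs per infection, T ≥ 0 the lifetime treatment cost per infection, and C the additional cost of PrEP use.

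ICER = (C − T·A) / (D·A)

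The only premise is C > 0. It is safe: PrEP adds monthly pickups and creatinine tests, and the microcosting counts in-kind contributions, so the donated drug is included. For A < 0:

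- Numerator: C − T·A = C + T·|A| > 0.
- Denominator: D·A < 0.
- ICER < 0, which is below GDP per capita, so the label is 'highly cost-effective'.
- Cost-saving would need C ≤ T·A, but T·A ≤ 0 < C, so that class does not catch the case.
- 'Not cost-effective' needs an ICER above 3 times GDP per capita, which a negative number cannot reach.

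At A = 0 the ratio is undefined and the rule gives no label.

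**2. Illustration of the reversed order.** The documents give no costs. Assume, in units of GDP per capita, 0.1 per person-year on PrEP, T = 2 and D = 10. With 620 person-years, C = 62.

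| A | ICER (GDP per DALY) | Label under the rule |
|---|---|---|
| 10 averted | (62 − 20)/100 = 0.42 | highly cost-effective |
| 1 averted | (62 − 2)/10 = 6.0 | not cost-effective |
| 1 extra infection | (62 + 2)/(−10) = −6.4 | highly cost-effective |
| 10 extra infections | (62 + 20)/(−100) = −0.82 | highly cost-effective |

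**3. The plan's own figure.** The article states no error rate for the cost-effectiveness rule, so the figure to reproduce is the 1240. Inputs are from Sample Size Calculation: 8.5 per 100 person-years, 50% reduction, power 0.8, one-sided alpha 0.025, and 10% standard-error inflation (the middle of the stated 0% to 20%). The Schoenfeld formula gives 4 × [(1.960 + 0.842) × 1.1 / ln 2]² ≈ 79 events. Average incidence is 0.085 × 0.75 = 0.06375 per person-year, and 79.05/0.06375 = 1240 person-years. This matches the 620 and 620 person-years in the Abstract, which are used below.

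**4. How often A is negative.** Take infections off PrEP as Poisson(0.085 × PY off) and on PrEP as Poisson(0.085 × HR × PY on), with A = off × (PY on / PY off) − on. At 620/620, expected infections off PrEP are 52.7. The 80/20 split (992/248) keeps the total at 1240 and reflects accrual in Results: 135 of 168 person-years, or 80%, were on PrEP by February 2019. Exact probabilities:

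| True hazard ratio | P(A < 0), 620/620 | P(A < 0), 992/248 |
|---|---|---|
| 0.5 (planned) | 0.1% | 1.0% |
| 1.0 | 48.1% | 50.0% |
| 1.5 | 98.8% | 97.0% |

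At a hazard ratio of 1 and 620/620, P(A = 0) is 3.9%. With a continuous adjusted ratio, ties vanish and P(A < 0) under no effect is about 50%. Every A < 0 result is labelled 'highly cost-effective' whatever C, T and D are, given C > 0.

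**5. What depends on assumed costs.** A positive estimate gets a favourable label when A ≥ C / (T + 3·GDP·D). Assume 200 to 1000 USD per person-year, T of 5,000 to 20,000 USD, D of 3 to 10 and GDP per capita of 6,000 USD. The total share of favourable verdicts at a hazard ratio of 1 and 620/620 is then 63% to 96%. With T = 5,000 and D = 3, raising the PrEP cost to 2,000 USD requires A ≥ 1,240,000/59,000 = 21.02, that is 22 infections, and the total is 49.9%. At 3,000 USD it is 48.2%.

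**The case against.** **The article is condensed.** It cites published recommendations for cost-effectiveness analysis, its language presupposes that infections and DALYs are averted, and dominance may be dealt with in a document not shown. That is a fair reason to treat this as a correction of wording. It does not remove the point, because the article does not leave the classes open. A general reference to recommendations does not alter the stated cut-offs.

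**The case is improbable under the design assumptions.** This stands. At the planned hazard ratio of 0.5, a negative estimate arises in about 0.1% of trials, or about 1% at an 80/20 split. A harmful ratio would also be plain in the primary analysis. But a decision rule is needed most when results disappoint, and Data Analysis itself warns that self-selection may bias the comparison.

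**Two stronger readings are tempting, and the documents do not support them.**

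- A reader might infer that with no PrEP effect the rule gives a favourable verdict most of the time. That rests on cost and DALY figures that the article does not give. The total is 63% to 96% over one assumed range but about 48% to 50% with costlier PrEP. Only the 48.1% with negative infections averted is the sign fault. The rest comes from small positive point estimates.
- A reader might infer that the sensitivity analyses would often meet the reversed label even when PrEP works, because the 95% interval for the hazard ratio can cross 1. The article does not say that this interval is the range used. It names primary data, literature and expert opinion as sources. It says that estimates will be reported, not that labels will be reassigned in each run.

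**Conclusion.** The point holds as a fault in a stated rule. Whenever estimated infections averted are negative and PrEP use costs more than nonuse, the rule labels a costlier and less effective result 'highly cost-effective', and no unfavourable class can be reached. The sign argument needs no outside figure.

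The size depends on the true effect: negligible at the planned one, close to half of trials with no effect, and nearly all at a hazard ratio of 1.5. These probabilities assume Poisson counts, 8.5 infections per 100 person-years and the full 1240 person-years. The same reversal would arise in a sensitivity analysis that takes infections averted below zero, if the labels are applied there.

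This concerns the decision rule of Aim 3 and leaves the primary HIV incidence comparison untouched. It does not show that the trial is likely to reach a wrong verdict.

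**What to change.** In Cost-Effectiveness Analysis:

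1. Keep the cost-saving class as it is.
2. Apply the 'highly cost-effective' and 'cost-effective' labels only when DALYs averted are positive.
3. Report a result with zero or negative DALYs averted and positive incremental cost as dominated, and hence not cost-effective.
4. Use the same rule wherever labels are applied in the sensitivity analyses.

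An equivalent form is incremental net benefit, (threshold × DALYs averted) − (additional intervention cost − treatment cost averted), evaluated at 1 and 3 times GDP per capita with the cost-saving class kept in front. Either form will do; the sign condition is the smaller edit.

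The cost is a sentence or two and trivial programming, with no new data. Results with positive DALYs averted keep their present class. The change removes the reversed label only. A rule based on a point estimate can still return a favourable verdict by chance when PrEP has no effect.

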### Ethical Review

The protocol, site-specific informed consent form, participant education and recruitment materials, and other requested documents—and any subsequent modifications—have been reviewed and approved by the following institutional review boards (IRBs) and ethical committees (ECs): Thailand Ministry of Public Health Ethical Review Committee for Research in Human Subjects; The US CDC IRB; and The Johns Hopkins Bloomberg School of Public Health IRB. The Emory University IRB defers to the Johns Hopkins University IRB, which has been documented by letter to the principal investigator (PI). The study protocol is also reviewed and approved by the Prevention Sciences Review Committee of the Division of AIDS, National Institute of Allergy and Infectious Diseases (NIAID)/National Institutes of Health (NIH; Multimedia Appendix 1).

### Safety Monitoring and Adverse Event Reporting

Study staff have established a data and safety monitoring plan. The staff ensure that interview protocols are followed, review all adverse event reports (if any) and ensure that confidentiality procedures are implemented. The larger project team meets regularly to discuss progress toward data collection goals. At these meetings, study staff prepare weekly reports on data collection and any emerging issues or potential problems regarding the Web-based survey data collection efforts.

The site PIs report in writing all serious adverse events associated with the study procedures and/or any incidents or problems involving the conduct of the study staff or subject participation, including problems with the consent processes, per IRB protocols. Drug-related adverse events described by study participants or identified during laboratory testing after initiation of Truvada (eg, nonbaseline abnormal creatinine levels) are collected and submitted to the Thailand MOPH EC, CDC IRB, and JHU IRB in accordance with individual IRB and EC requirements, and to the Thai Food and Drug Administration as per their requirements. Adverse events severity is graded following sponsor guidelines [49]. Study participants are provided instructions for contacting the study site staff to report any negative medical occurrences they may experience. Where feasible and medically appropriate, participants are encouraged to seek evaluation where a study clinician is based; in the event this is not possible, and participants receive care elsewhere, they are asked to follow-up at SCC @TropMed for further evaluation and determination whether adverse-event reporting is necessary.

In the context of this effectiveness study of an approved drug (tenofovir and FTC) in Thailand, adverse events, should they occur, are likely to be the social harms associated with disclosure of status as an MSM or TGW, a sex worker, as having HIV infection or at risk for HIV infection, or as being on PrEP. The study team regularly assesses each of these social harms through the surveys, at monthly PrEP medicine pickups, and through regular meetings with the community advisory board. Study staff are trained on social harm counseling and monitoring before study initiation and undertake additional efforts to minimize social harms to participants. Study staff record information pertaining to the event on the Social Harm Case Report Form and provide counseling with proposed solutions or refer participants to personnel or organizations with this specific expertise. Study staff make every effort to provide appropriate care and counseling to the participant and offer referral to appropriate resources, as needed, for the participant’s safety. Study staff follow up about the social harm event at every study visit and record updated information onto the Social Harm Case Report Form. Social harms that are determined by the study investigators to be serious or unanticipated are reported to the responsible IRBs, or according to their individual IRB requirements.

